**LABOR COSTS (time spent on…)**			
Depression care services	2,3,4	Monthly labor worksheet	Wage rates
Community outreach activities	2,3,4	Monthly labor worksheet	Wage rates
Planning activities	1,2,3	Monthly labor worksheet	Wage rates
Training activities	2,3,4	Attendance sheets	Wage rates
Monitoring/supervision activities	2,3,4	Supervisor logs	Wage rates
Learning collaborative activities	1,2,3,4	Attendance sheets	Wage rates
Providing technical assistance	1	Supervisor logs	Wage rates
***SUPPLIES***			
Cost of workshop/training materials including toolkit, outreach materials, etc.	1,2	Hanoi University of Public Health accounting records	List price
Food, copies, stationary, other equipment, medications	1,2,3	Monthly accounting records	Local prices
***MISCELLANEOUS COSTS***			
Travel	1,2,3,4	Weekly logs, travel reimbursement	Mileage rates
Lodging	1,2	Weekly logs	Prices paid
***OVERHEAD (INDIRECT) COSTS***			
Capital costs - Space for meetings (sq. feet) - Equipment (e.g., computers)	1,2,3	Weekly logs Key informant interviews	Rental rates
***CLIENT PARTICIPATION COSTS***			
Client time	5	Key informant interviews	Avg income
Client travel	5	key informant interviews	Local prices
Treatment cost	3,5	Invoices, key informant interviews	Service rates

**Key Code**: 1: Project staff providing TA; 2: Local implementation staff; 3: CHS staff members; 4: non-CHS participants in the community collaborative; 5: Clients

We will estimate the incremental cost-effectiveness ratio (ICER) of ES and CELC relative to UI of depression care, defined as the incremental change in costs relative to the incremental change in effectiveness (e.g., QALYs with ES/CELC minus QALYs with UI alone). Effectiveness will be measured based on (1) adoption rate (measured as proportion of trained providers delivering MCCD components); (2) implementation quality measured by average fidelity score; (3) reach (measured as proportion of eligible clients getting treated); (4) effectiveness (measured by client outcomes by using average PHQ-9 scores, work days missed, and QALYs); and (5) maintenance (measured as adoption, reach, implementation quality, and effectiveness at 24 months).

To examine the ICER for each enhanced implementation strategy, a Markov modeling framework [62] will be utilized to estimate the relative costs and outcomes of clients enrolled in each of the three trial arms, with UI serving as the base case by which to compare alternative implementation frameworks. A Markov chain Monte Carlo approach with 100,000 simulations will also be utilized for sensitivity analyses, in which we systematically examine the extent to which variation in cost and implementation parameters affect estimated ICERs.

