**Discussion:**

We hypothesize that the additional implementation supports will make mental health service implementation superior in the ES and CELC arms compared to the UI arm. The findings of this project could identify effective implementation models and assess the added value of specific QI strategies for implementing depression care in primary care settings in Vietnam, with implications and recommendations for other low- and middle-income settings. More importantly, this study will provide evidence for key stakeholders and policymakers to consider policies that disseminate, scale up, and advance quality mental health care in Vietnam.

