### Arm 3: community-engaged learning collaborative (CELC)

CHS Providers will receive all components of the ES group, plus a new quality improvement (QI) strategy: CELC. The CELC meetings will be based on the community engagement and planning implementation intervention model in Community Partner in Care [35, 38, 46] and the CELC from the Institute for Healthcare Improvement (IHI) Chronic Care Model [47]. The IHI model includes key components like forming a planning group that decides on a mutual set of target objectives, identifies specific areas for change, prepares pre-work with participants, implements in-person learning sessions. During CELC meetings, CHS staff and their supervisors learn about QI approaches and strategies on how to provide effective ongoing support to clients (e.g., phone calls, visits, messaging via apps, social media). Between each learning session, the CELC groups engage in Plan-Do-Study-Act (PDSA) cycles in which they brainstorm and decide on brief CHS-level interventions aiming to improve certain clinical processes at the CHS or meeting certain treatment benchmarks and assess their impact afterward [48]. Because of the resource intensity of the IHI model, we will adapt and simplify the approach in partnership with the community-academic-policy council to develop a learning collaborative (LC) that is feasible and culturally appropriate for the Vietnam health and social system. For example, QI learning collaboratives tend to last between 1 and 2 years [49], but we will only have nine meetings that are strategically placed to maximize implementation support.

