### Outcome evaluation and analysis for AIM 1 (Fidelity to MCCD)

#### Power analysis

We used the pwr package in R software to determine the sample size and estimate power to detect a small eta-squared effect size of 0.025 with an expected intra-class correlation coefficient (ICC) of 0.2. Our primary outcome analyses focus on the 12-month timepoint, we will enroll 10 providers per site resulting a total of 360 providers (180 CHS staff and 180 non-CHS staff) across 36 sites in order to achieve 80% power to detect the small effect size. We also enroll 18 clients per site per phase which results in a total of 648 clients over two phases. With client outcome, power calculations assume near-normal outcomes with a two-sided Type I error of 0.05, this design has 80% power to detect small effects (small Cohen’s d effect size of 0.14 for a 3 × 3 contingency table chi-square test, given 4 degrees of freedom [(3 intervention groups {UI, UI + ES, UI + ES + CELC} − 1)*(3 outcome levels of PHQ-9 score change from baseline to 6 months {positive change, no change, negative change} − 1)]).

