#### RE-AIM outcomes

According to the RE-AIM framework, for an intervention to have an impact, it must **Reach** the population in need of the service, demonstrate **Effectiveness**, be **Adopted** by the system and providers, be **Implemented** with quality, and be **Maintained** or sustained over time. The indicators’ description as well as data sources were presented in detail in Table 1. A cascade of MH care will be built based on these indicators (Fig. 2). Mean and standard deviation will be presented without the normality violation, otherwise, median and interquartile ranges will be used. Independent ANOVA and/or Kruskal-Wallis test will be applied to assess differences stratified by intervention arms.

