#### Client outcomes

Clients identified with depression as part of routine depression screening at CHS will be recruited to participate in the client outcomes survey study across two implementation support phases. Eligible clients included those who are (1) new to the program, (2) aged 18–65, and (3) screened positive for depression using the PHQ-9 (score > 9). Those with a risk for severe mental illness (psychosis, mania, and substance abuse) will be excluded from the Client Study Cohort and referred to the provincial psychiatric hospital, per the stepped care model mentioned in the intervention description. Based on a depression screening rate of 20% and a research acceptance rate of 75% from our prior work [20], we expect CHS staff to screen 2,200 clients to consent 324 participants across each province for each Client Study Cohort. Across the total sample of 648 clients in each implementation phase. We will request permission from participants to link survey data to client administrative and clinical data.

The effectiveness on the client outcome will be measured based on the client’s improvement (defined as a 50% reduction in PHQ-9 score between the first and last BA session) and client’s remission (defined as the last PHQ-9 score less than 5). We will conduct an intent-to-treat analysis (e.g., those who are lost to follow-up are considered neither improved nor remised) in order to ensure the randomization process. A generalized linear mixed-effects model will be used for binary outcomes with a binominal family distribution and logit link. Exponentiating the fix-effect coefficients for treatment conditions will result in estimates of the odds ratio regarding the effect of treatment condition on depression symptomatology. These models will be adjusted for the clustering effects across multiple levels of hierarchical data structure (e.g., providers, clients) and the UI intervention will be used as a reference group.

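### Aim 3 defines both ICERs against usual implementation only, so CELC can look cost-effective when the step from enhanced supervision to CELC is not

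*Protocol article*

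**What the plan says.** The section on outcome evaluation and analysis for Aim 3 sets the comparator three times. It states: "We will estimate the incremental cost-effectiveness ratio (ICER) of ES and CELC relative to UI of depression care". It gives the denominator, as an example, as "QALYs with ES/CELC minus QALYs with UI alone". It then describes a Markov model covering all three arms, "with UI serving as the base case by which to compare alternative implementation frameworks". The Abstract (Methods) and the last paragraph of the Background describe the economic aim in the same way, with UI as the comparator for both other arms.

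The arms build on one another. The Arm 3 section says: "CHS Providers will receive all components of the ES group, plus a new quality improvement (QI) strategy: CELC". The Arm 2 section builds ES on UI in the same manner.

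The stated purpose is wider than a comparison with UI. The Abstract (Discussion) says the project could "assess the added value of specific QI strategies for implementing depression care". The intervention description and the main Discussion both list as unresolved what supervision and learning collaboratives each contribute. The main Discussion also says the study will help find the strategy that is best on effectiveness and cost.

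On the effectiveness side, the Client outcomes section says of the mixed models for improvement and remission that "the UI intervention will be used as a reference group". The RE-AIM outcomes section names no reference arm: "Independent ANOVA and/or Kruskal-Wallis test will be applied to assess differences stratified by intervention arms".

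**The concern.** When options are mutually exclusive and each contains the one before, the decision is whether each further step is worth its extra cost. The ratio that answers this compares each option with the next less costly one that has not been ruled out. CELC versus UI does not do that. It credits CELC with whatever supervision achieves, although ES already delivers supervision without the cost of the collaborative.

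The consequence falls on the trial's main policy output. A health department could read a favourable CELC-versus-UI ratio as a reason to fund learning collaboratives, when most of the benefit behind it came from supervision. The table of planned ratios would not show this, because the article does not call for the ES-to-CELC ratio.

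**Working it through.** **Inputs.** From the document: the comparator (UI for both ICERs), the nesting of the arms, and the fact that all three arms are modelled. It states no cost, QALY gain or willingness-to-pay threshold and no ICER, so there is no plan figure to reproduce. All cost and QALY values below are assumptions.

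**Formula.** Write ΔC and ΔE for increments over UI.

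- ES vs UI = ΔC(ES) / ΔE(ES)
- CELC vs UI = ΔC(CELC) / ΔE(CELC)
- CELC vs ES = [ΔC(CELC) − ΔC(ES)] / [ΔE(CELC) − ΔE(ES)]

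When both steps add benefit, CELC vs UI = w × (ES vs UI) + (1 − w) × (CELC vs ES), with w = ΔE(ES)/ΔE(CELC). The planned CELC ratio is therefore an effect-weighted average of the two steps. It lies below the ratio for the second step whenever the second step is less efficient than the first.

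**Assumed values.** Cost +100 for ES and +180 for CELC, so the step costs 80. QALY gain 0.020 for ES, so ES vs UI = 100/0.020 = 5,000. The CELC gain is varied:

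| CELC gain over UI | CELC vs UI (planned) | CELC vs ES (not planned) |
|---|---|---|
| 0.036 | 180/0.036 = 5,000 | 80/0.016 = 5,000 |
| 0.030 | 180/0.030 = 6,000 | 80/0.010 = 8,000 |
| 0.024 | 180/0.024 = 7,500 | 80/0.004 = 20,000 |
| 0.020 | 180/0.020 = 9,000 | 80 for no gain: ES dominates CELC |
| 0.018 | 180/0.018 = 10,000 | 80 for a loss of 0.002: ES dominates CELC |

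Check of the average at 0.024: w = 0.020/0.024 = 5/6, and 5/6 × 5,000 + 1/6 × 20,000 = 7,500.

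**Effect on the decision.** At a CELC gain of 0.024, any threshold between 7,500 and 20,000 passes CELC against UI while the added step fails. With an assumed threshold of 10,000, net benefit over UI is 10,000 × 0.020 − 100 = 100 for ES and 10,000 × 0.024 − 180 = 60 for CELC. ES is the better choice, although both planned ICERs pass.

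**The other direction.** Keep the costs and take gains of 0.010 for ES and 0.030 for CELC. Then ES vs UI = 10,000, CELC vs UI = 6,000 and CELC vs ES = 80/0.020 = 4,000. Here ES is extendedly dominated, and CELC vs UI is the relevant ratio. A full incremental analysis reaches that result by its own rules.

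**What the trial is sized for.** The client calculation in the Power analysis section is an omnibus one: "small Cohen’s d effect size of 0.14 for a 3 × 3 contingency table chi-square test, given 4 degrees of freedom". With 648 clients the noncentrality is 648 × 0.14² = 12.70, which gives 82.7% power. The effect detectable with 80% power is 0.136, which rounds to the stated 0.14. This is before any allowance for clustering, and it does not size an ES–CELC contrast.

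**The case against.** The strongest reply is that the plan does what its hypothesis and economic aim say. The Abstract hypothesises that ES and CELC each do better than UI, and the Background frames cost-effectiveness relative to UI. Added value can also be read as value over usual implementation. This stands as far as the hypothesis goes. It does not meet the separate promise to separate the contributions of supervision and collaboratives and to find the most cost-efficient strategy, which requires the ES-to-CELC step.

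A reader might infer that the ES–CELC difference can never be estimated, or that the trial will end unable to say what the collaborative adds. The document does not support this. The Markov model covers all three arms, so the difference between CELC and ES follows from its output. In the client model UI is only the coding reference, and the CELC and ES coefficients can be differenced. What is missing is a pre-stated contrast.

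A reader might also infer that every effect analysis is against UI alone. UI is named as reference only in the client model. The RE-AIM tests are three-arm omnibus tests, which include the ES–CELC difference without isolating it. Pairwise follow-up contrasts are often left to an analysis plan, so this side of the matter is a minor note. That allowance does not cover Aim 3, where the comparator is written out.

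Lastly, the distortion is conditional. It does not arise if the collaborative step is as efficient as supervision or more so.

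**Conclusion.** The point holds for Aim 3. Fixing UI as the comparator for both ICERs does not suit three nested, mutually exclusive strategies when the stated purpose is to choose among them.

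The size is unknown, because the document gives no costs, QALYs or threshold. Under the assumed costs and an ES gain of 0.020 QALY, the step ratio runs from equal to the planned CELC ratio (5,000 each), through 8,000 against 6,000 and 20,000 against 7,500, to outright dominance by ES while the planned ratio reads 9,000. A reader might take one of these rows as the expected distortion. None of them is a forecast. The direction depends only on whether the second step is less efficient than the first, which the trial has yet to show.

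For the client effect model the conclusion is weaker: the CELC-versus-ES contrast is derivable but not pre-stated.

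**What to change.** In the Aim 3 section, replace the UI-only rule with a full incremental analysis. Order the three arms by cost, remove dominated and extendedly dominated arms, and report each remaining arm against the next best, which is CELC versus ES whenever ES remains. Keep ES versus UI and CELC versus UI as supplementary results. State the CELC-minus-ES differences in cost and effect in every case, since they answer the added-value question even if an arm is removed. The planned simulations can carry the uncertainty for all three arms together.

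As a minor addition in the Client outcomes section, pre-state CELC versus ES, with its confidence interval, as a further contrast from the same fitted model.

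The cost is wording plus one extra contrast to report. No new data, sites or model are needed, and Table 2 already records supervision and learning-collaborative labour on separate lines. The drawback is that the ES–CELC estimate will probably be imprecise, because the trial is not sized for it. It should be presented as an estimate with its interval, and an inconclusive result should not be read as showing no difference.

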### Ethical considerations

This study was approved by the Institutional Review Board at the Graduate School of Public Health and Health Policy, The City University of New York, U.S. and The Hanoi University of Public Health in Vietnam.

### Trial status

As of December 2022, we successfully recruited 18 CHSs and provided training to 5 provincial supervisors, 6 district supervisors, 90 CHS staff and 90 non-CHS staff in Bac Giang through a combination of in-person training and Moodle online learning platform. All providers underwent assessments before and after the training. During the phase 1 of the project, we interviewed 324 clients and completed collecting a 6-month follow-up survey for CHS and non-CHS providers. The recruitment of an additional 18 CHSs in Phu Tho will continue in 2023.

## Discussion

Depression is a prevalent and debilitating MH condition that affects people in nearly every country, including Vietnam, and is one of the largest burdens of health [63]. Although effective treatments exist, many with depression do not receive appropriate care [64]. The treatment gap is significantly expanding, especially during the COVID-19 pandemic when global prevalence of depression and anxiety increased by 27.6% and 25.6%, respectively [65]. Likewise, the Vietnamese population experienced a depression burden during the pandemic with six times higher compared to prior period (14.6% vs. 2.5%, respectively) and if these disorders are not addressed appropriately, the community will suffer from significant long-term mental social and economic consequences [66]. Yet, previous MH interventions have primarily targeted high-risk groups such as hospital nurses [67], people who inject drugs [68], caregivers [69], and cancer clients [70]. There are only two RCTs with small sample sizes conducted in the primary care centers [71, 72]. Hence, in order to significantly close the treatment gap as well as sustain treatment for depression, effective depression care programs with a large sample size need to be piloted and scaled up to a wider network of community health stations that are supported by the local psychiatric hospitals.

In response to the increasing recognition of the need to address the treatment gap for depression, Vietnam developed a national plan on MH disorders for the period 2022–2025. The strategy adopts a community-engaged multi-sectoral approach to promote evidence-informed policies and practices to improve MH care [73]. This national strategy focused on implementing key activities, aligning financial resources for MH human resources and infrastructure, building capacity, developing research, information technology, and multi-sectoral coordination mechanisms to achieve its goals. This study directly addresses a pressing issue not only in Vietnam but also within the costly international health crisis during the COVID-19 pandemic. This study, therefore, will play a key role in finding the most effective and cost-efficient strategy for integrating MH care with primary health care in vulnerable and resourced-limited communities.

Our previous work has developed a task-shifting MH care model called the MCCD program, which was proven effective according to an RCT conducted in Da Nang and Khanh Hoa provinces [20]. The model provides psychotherapy for a 2–3 month period and can be delivered by CHS nurses, physicians, and other community health workers who are supervised by local psychiatrists. The study findings suggest that collaborative care for depression can be task-shifted to primary health and community health providers with minimal support from MH specialists. However, the optimal implementation model for supporting depression care in primary care settings, the added value and effectiveness of adding additional implementation supports such as enhanced supervision and community-engaged learning collaboratives, and factors influencing adoption, implementation quality, and sustainability when scaling depression care are not yet clear. So, this study will address the gap by: (1) enhancing intersectoral collaboration and community engagement, (2) increasing capacity to detect and treat MH conditions, particularly depression, in primary care settings, and (3) strengthening information systems, evidence, and research on MH in low-resource settings.

There are several limitations to our study. COVID-19 posed significant challenges to successful implementation of this protocol. Firstly, the COVID-19 pandemic began during the study, causing the transition of in-person training to hybrid training to comply with social distancing policies and travel limitations. The U.S. study staff were unable to support on-site providers in terms of training and practicing key skills in person. Although, CHS providers were able to practice BA in person with clients—the main psychoeducation method in this study, they did not receive direct supervision. This barrier might have a small impact on providers’ skills since their sessions were recorded and provided with feedback during consultation calls. Therefore, project staff along with provincial and district supervisors could help them identify strengths and weaknesses for psychotherapy practices. Another limitation was the limited availability of appropriate staffing due to the deployment of healthcare staff to national COVID-19 testing and vaccination programs in various provinces. However, after training was completed virtually and in-person, the intervention ran smoothly and did not appear to impact implementation of the program. Lastly, our intervention is conducted in two mountainous and rural areas, which limit the ability to compare the effectiveness of depression care program in rural and urban areas. However, the Vietnam healthcare system follows a hierarchal structure, and findings from this intervention—will provide decision-makers with evidence bases about what could be achieved if they enacted strategic adjustments in their approach to health service delivery—could be applicable to other provinces over the country. Again, despite these limitations, the findings of this project hold high implications by identifying best practices for implementing depression care in primary care settings in Vietnam and other low- and middle-income countries. More importantly, this study will provide evidence bases for key stakeholders and policymakers to make decision towards scale-up as well as dissemination of MH care guidelines.

